**Table 1 Tab1:**
[figure not shown]
Angina pectoris subscale

**Table 2 Tab2:** Coronary heart disease Chinese medicine main symptom scale

Symptom	Symptom grading score
**Chest pain**	☐ 0 points: None.
	☐ 3 points: Remission after rest will not affect daily life.
	☐ 6 points: medication is required at the time of onset, and normal life can be continued after remission.
	☐ 9 points: Frequent seizures affect daily activities (such as dressing, eating, walking, and large symptoms can be induced).
**Chest tightness**	☐ 0 points: None.
	☐ 3 points: I feel a chest tightness and can relieve myself.
	☐ 6 points: Chest tightness attacks are more frequent, but do not affect normal life and work.
	☐ 9 points: Chest tightness continues to be incomprehensible, affecting life and work.
**Shortness of breath**	☐ 0 points: None.
	☐ 2 points: short after the event.
	☐ 4 points: A little move is short.
	☐ 6 points: I usually feel short of breath.
**Weak**	☐ 0 points: None.
	☐ 2 points: Severe activity is weak.
	☐ 4 points: Moderate activity is weak.
	☐ 6 points: Mild activity is weak.
**Heart palpitations**	☐ 0 points: None.
	☐ 1 point: Occasionally, you can relieve yourself.
	☐ 2 points: Frequent attacks, but can persist at work.
	☐ 3 points: The heart is constantly puzzled, affecting life and work.

### Secondary outcome measures

The following measurements will also be taken; blood lipid levels; B-type natriuretic peptide (BNP); troponin (cTn); muscle enzyme isoenzyme (CK-MB); heart-type fatty acid binding protein (H-FABP); and electrocardiogram.

### Safety outcomes

These are vital signs including blood, urine, and fecal routines, liver and renal functions as well as coagulation. These indicators will be closely monitored during this process.

### Observation records of adverse events

Any adverse events that occur during the course of the trial, including laboratory abnormalities, must be carefully interrogated and tracked. We will therefore judge these events by their nature, severity, and drug relevance and strictly record their outcomes in the case report form.

### Research process record points

The subject content and data at each time point, according to the patient’s hospitalization period, will be recorded as shown in Fig. 2. Specifically, the screening period (0 days) will be 24 h before recruitment followed by a daily data tracking and recording from day 1 to day 7, and a follow-up on day 28 after treatment is administered.

**Fig. 2 Fig2:**
[figure not shown]
Content and points of data capture

### Statistical analysis

Statistical analysis will be performed using SPSS 19.0 statistical software. Measured data will be described using means and standard deviation of the mean, while count data will be by the number of cases in percentages. First, a baseline analysis of the demographic characteristics in the four groups of selected cases will be conducted to investigate the balance and comparability across groups. Then, the effectiveness and safety indices will be compared across the four groups. The comparison of iso-quantitative data between the experimental and the control group will be performed using a student *t*-test of two-sample comparison for group design, while the comparison of the two classification indicators such as gender will be performed using the Cochran-Mantel-Haenszel χ^2^ test or Fisher’s exact probability method. The missing supplementary data will be adjusted using imputation methods. To validate ineffectiveness among the groups, we will perform a rank sum test of the two-sample comparison in the groups. All statistical tests will be two-sided with *p* ≤ 0.05 to be used for statistical significance.

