### Sample size

This study will use a parallel design of randomized controlled trials and hs-CRP as the main effect index. Conventional Western medicine treatment can reduce hs-CRP by 32%, according to clinical conditions, and it is estimated that Chinese medicine can reduce hs-CRP by 52%. The set α = 0.025, β = 0.2, superiority limit value δ = 20%, and the sample size of each group will be calculated as 30 cases [16, 17]. Considering the loss of follow-up, 40 patients with stable coronary heart disease and 160 with four combinations will be selected.

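### The planned t-test for hs-CRP and the cytokines names no baseline term and no log scale, so it is valid but inefficient for a proportional effect, and the rank-sum test beside it has no defined role

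*Protocol article*

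**What the plan says.** All of this is in the Protocol article; the statistical analysis plan is not shown.

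- **Summary (Statistical analysis).** "Measured data will be described using means and standard deviation of the mean". I read this as mean and ordinary SD. No median, interquartile range or geometric mean is mentioned.
- **Test (Statistical analysis).** "The comparison of iso-quantitative data between the experimental and the control group will be performed using a student" two-sample t-test. No covariate, transformation or distribution check is attached. The text does not say whether the variable tested is the post-treatment value, the change or the percent change.
- **Baseline (Statistical analysis).** The one stated use is a balance check: "a baseline analysis of the demographic characteristics in the four groups of selected cases will be conducted".
- **Rank-sum test (Statistical analysis).** "To validate ineffectiveness among the groups, we will perform a rank sum test of the two-sample comparison in the groups". No outcome is named.
- **Effect (Sample size).** The trial takes "hs-CRP as the main effect index". It says "Conventional Western medicine treatment can reduce hs-CRP by 32" per cent and expects a 52 per cent reduction on the Chinese medicine.
- **Visits (Research process record points).** "the screening period (0 days) will be 24 h before recruitment followed by a daily data tracking and recording from day 1 to day 7". What is measured at each visit is in Fig. 2, which is not reproduced in the text at hand.

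**The concern.** A percentage reduction is a multiplicative effect measured from a baseline. The natural estimate is a ratio of post-treatment levels between arms, adjusted for each patient's starting level. The stated test compares arithmetic means and has no place for the starting level as a covariate. If the markers are right-skewed, as positive serum concentrations often are, a few high values can dominate the mean of 30 to 40 patients.

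What is at stake is precision on the outcome the trial is sized for. A second issue is how results will be read. A rank-sum test with no assigned outcome permits a second, possibly conflicting, p-value on hs-CRP. Its stated purpose is also one it cannot serve, because failing to reject a null hypothesis does not establish that a treatment lacks effect.

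**Working it through.** **1. The plan's own figure.** The Sample size section gives 30 per group (40 after allowance for loss) from 32% v 52%, α = 0.025, β = 0.2 and δ = 20%. It does not reproduce from these inputs.

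- Read as two proportions, 0.32 v 0.52 needs 95 per group (one-sided 0.025, no continuity correction).
- With δ equal to the expected 20-point difference, the superiority denominator is 20 − 20 = 0 and no finite n exists.
- Read as means, n = 2(1.96 + 0.842)²σ²/20² = 30 requires σ of about 27.6 percentage points, which is not stated.

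The article therefore gives no SD from which to derive absolute power. Below, 30 per arm is taken as given and the unknown quantities are varied.

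**2. Target effect.** The ratio of post-treatment levels is (1 − 0.52)/(1 − 0.32) = 0.48/0.68 = 0.706.

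**3. Closed form: adjustment alone, no skewness.** Suppose 30 per arm gives exactly 80% power for the unadjusted test. Analysis of covariance multiplies the variance by 1 − r² relative to a t-test on post-treatment values, and by (1 + r)/2 relative to a t-test on change. Power = Φ(2.802/√factor − 1.96).

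| r | Factor v post | Power | Factor v change | Power |
|---|---|---|---|---|
| 0.3 | 0.91 | 0.836 | 0.65 | 0.935 |
| 0.5 | 0.75 | 0.899 | 0.75 | 0.899 |
| 0.7 | 0.51 | 0.975 | 0.85 | 0.860 |

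**4. Simulation with skewness.** Log-normal marker, 30 per arm, true ratio 0.706, two-sided 0.05 as in the Statistical analysis section, 8,000 trials per setting. Log-SD and r are assumptions. Entries are power.

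| Log-SD | r | t, post value | t, change | t, percent change | Rank-sum, post | Log ANCOVA | Gain v post (points) | Gain v percent change (points) |
|---|---|---|---|---|---|---|---|---|
| 0.5 | 0.3 | 0.705 | 0.311 | 0.551 | 0.730 | 0.787 | 8 | 24 |
| 0.5 | 0.5 | 0.713 | 0.370 | 0.699 | 0.739 | 0.864 | 15 | 17 |
| 0.5 | 0.7 | 0.702 | 0.502 | 0.910 | 0.732 | 0.954 | 25 | 4 |
| 0.8 | 0.3 | 0.303 | 0.134 | 0.205 | 0.358 | 0.403 | 10 | 20 |
| 0.8 | 0.5 | 0.299 | 0.154 | 0.296 | 0.355 | 0.471 | 17 | 18 |
| 0.8 | 0.7 | 0.306 | 0.201 | 0.496 | 0.369 | 0.633 | 33 | 14 |
| 1.0 | 0.3 | 0.184 | 0.095 | 0.119 | 0.253 | 0.283 | 10 | 16 |
| 1.0 | 0.5 | 0.189 | 0.103 | 0.184 | 0.266 | 0.335 | 15 | 15 |
| 1.0 | 0.7 | 0.178 | 0.129 | 0.322 | 0.246 | 0.453 | 28 | 13 |

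Log-scale ANCOVA has the highest power in every row. The gain over a post-value t-test is 8 to 33 points. Over a percent-change t-test it is 4 to 24 points in this table; a repeat of the simulation put the upper end at 26, so the range is stated as about 4 to 26. The t-test on absolute change does worse than either.

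**5. Validity.** With no treatment effect (r = 0.5), the three raw-scale t-tests rejected in 0.041 to 0.051 of trials. The cost is power and interpretability, not false positives.

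**The case against.** The strongest defence is that nothing here is invalid. Randomisation makes the unadjusted comparison unbiased, its standard error already reflects chance baseline imbalance, and type I error held in the simulation. Transformation and covariates are often left to the analysis plan. The first part stands. The second does not dispose of the point, because the article names a specific test, and an analysis plan that followed it would carry the same inefficiency.

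Four stronger readings are tempting, and the article does not support them:

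- **That baseline is ignored.** The variable entering the t-test is not stated. Because the effect is framed as a percentage reduction, change or percent change is a natural reading, and either uses baseline, though less efficiently than a covariate does. That hs-CRP is drawn at day 0 is implied by that framing, not shown in the visible text. For the cytokines even this implication is absent.
- **That skewness is ignored.** A rank-sum test, which needs no normality, is also planned. The fair criticism is that its role is undefined. At log-SD 0.8 and r = 0.5 it has power 0.36, against 0.30 for the post-value t-test and 0.47 for log ANCOVA.
- **That much of the power is thrown away.** The article gives no SD, skewness or correlation. At r = 0.3 the closed-form gain over a post-value test is under 4 points.
- **That a non-significant rank-sum result would be reported as proof of no effect.** The sentence may be a mistranslation, and no such reporting rule appears. What stands is that the stated purpose cannot be met and needs correcting.

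**Conclusion.** The point holds as a recommendation on efficiency and clarity. The stated test is valid but does not match the proportional effect on which the trial is sized, and log-scale analysis of covariance was more powerful in every setting examined.

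The size of the gain rests on a log-normal marker, log-SD 0.5 to 1.0, baseline correlation 0.3 to 0.7, 30 analysable patients per arm and a ratio of 0.71. Only the 30 and the ratio come from the article. A reader might infer a known, large loss of power or a wrong result; neither can be shown from the document.

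The rank-sum point needs no assumption: as written, the test has no named outcome and a purpose that a non-significant result cannot fulfil.

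**What to change.** 1. Analyse log(hs-CRP) at the one time point named in advance as primary, using a linear model with treatment arm and log(baseline hs-CRP). Report ratios of geometric means with 95% confidence intervals.
2. Do the same for the cytokines and other skewed markers wherever a day-0 value is drawn.
3. Summarise these markers by geometric mean, or by median and interquartile range.
4. Restrict the rank-sum test to the ordinal outcomes (angina grade and symptom items).
5. Delete the phrase about validating ineffectiveness, and judge lack of effect from the confidence interval.

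Cost: wording only, with no new data, provided hs-CRP is drawn at day 0 as the percentage reduction in the Sample size section implies. Check this against the visit schedule in Fig. 2.

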Coronary heart disease is categorized as “chest pain” and “heartache” in Traditional Chinese Medicine (TCM), which plays an important role in its diagnosis and treatment. In particular, the “Yiqihuoxue” is the most widely used method for managing the condition [8]. Among the components therein, astragalus and Salvia are the most commonly used compatibility drugs. In our previous studies, we focused on investigating the roles of TCM in CHD [9–12]. In particular, it is evident that astragalus membranaceus, the main component of astragalus membranaceus, and tanshinone IIA, the main component of *Salvia miltiorrhiza*, can effectively improve myocardial ischemic injury [13]. Functionally, the mechanism of action of the Salvia miltiorrhiza is related to inhibition of cell inflammatory reaction and apop-tosis in myocardial ischemic injury [14].

Based on the above understanding, we hypothesize, from a clinical perspective, that individual astragalus and *Salvia miltiorrhiza* injections, or a combination of the two, have certain anti-inflammatory properties and could play a role in the treatment of CHD. We therefore aim to explore the effects of *Salvia miltiorrhiza* treatment on stable CHD and provide the basis for its clinical application.

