## Methods/design

### Study design and settings

The present study will be set up using randomly blinded and single-center experiments. We will recruit 160 patients who meet the eligibility criteria at the Guangdong Provincial Hospital of Traditional Chinese Medicine. Subsequently, the participants will be divided into four equal groups: three groups with treatment (treatment group A will receive conventional drugs plus astragalus injection treatment, group B will receive conventional drugs plus *Salvia miltiorrhiza* injection, and group C will receive conventional drugs plus *Salvia miltiorrhiza* and astragalus injections) and the control group will receive conventional drugs plus 0.9% NaCl injection. The study design is as illustrated in Fig. 1.

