### Objectives

This study intends to explore the effects of astragalus and *Salvia miltiorrhiza* injections as well as a synergistic treatment (of the two components) on stable CHD from the anti-inflammatory advantage and provide the basis for its clinical application.

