In our previous studies, we found that the main components of astragalus, astragaloside IV, *Salvia viltiorrhiza*, and tanshinone IIA can effectively improve myocardial ischemic injury [13, 26]. Functionally, the mechanism of action of these drugs targeted cellular inflammation in myocardial ischemic injury and inhibited death. However, from a clinical point of view, it remains unclear whether individual astragalus and *Salvia miltiorrhiza* injections, or a combination of the two, result in significantly different anti-inflammatory properties, during the treatment of CHD. This study will explore the effects of the astragalus injection, the *Salvia miltiorrhiza* injection, and their synergistic treatment on stable CHD from the anti-inflammatory advantage, and provide the basis and basis for its clinical application.

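### No interaction test or combination-versus-single contrast is specified or powered, although the Objectives and Discussion raise synergy and a difference between single and combined injections

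*Protocol article*

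**What the plan says.** **Design.** Under Study design and settings, "the participants will be divided into four equal groups": group A receives astragalus injection, group B *Salvia miltiorrhiza* injection, group C both, and the control group neither, all on top of conventional drugs.

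**Questions posed.** The article asks more than one thing.
- Background: the hypothesis is that each injection alone, or the two together, "have certain anti-inflammatory properties and could play a role in the treatment of CHD".
- Objectives: the study is to explore the effects of the two "injections as well as a synergistic treatment (of the two components) on stable CHD from the anti-inflammatory advantage".
- Discussion: it is called unclear whether the individual "injections, or a combination of the two, result in significantly different anti-inflammatory properties", and the study is said to explore this.

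**Tests named.** The Statistical analysis section begins generally: "Then, the effectiveness and safety indices will be compared across the four groups". No test or contrast is attached to that sentence. For quantitative data it then becomes specific: "The comparison of iso-quantitative data between the experimental and the control group will be performed using a student" t-test for two samples. A two-sample rank sum test is also planned, without saying which pairs of groups it compares. Tests are two-sided at 0.05.

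**Sample size.** hs-CRP is the main effect index. The assumptions are a 32% reduction on conventional treatment and one value, 52%, for Chinese medicine, giving 30 per group, raised to 40 per group and 160 in total. There is no separate value for the combination.

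**The concern.** The three questions need different contrasts. Whether an injection has an anti-inflammatory effect is answered by each arm against control. Whether the combination is better than a single injection needs C against A and C against B. Whether the two are synergistic needs the interaction, C − A − B + control. The specific part of the analysis section and the sample size cover only the first.

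What is at stake is what the report may claim. If C differs from control and A or B does not, that pattern does not show that C differs from A or B, because the difference between a significant and a non-significant result has not itself been tested. It says nothing about whether the joint effect exceeds the sum of the separate effects. The four-arm layout can supply both answers, so leaving the contrasts unnamed wastes information the trial will already hold.

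**Working it through.** **1. Questions against named tests**

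| Question | Contrast needed | Named in Statistical analysis? | Covered in Sample size? |
|---|---|---|---|
| Effect of A, B or C (Background) | arm − control | Yes, two-sample t-test | Yes, 52% v 32% |
| Combination v single (Discussion) | C − A and C − B | Not named; the four-group sentence or the rank sum test might cover it | No |
| Synergy (Objectives, Discussion) | C − A − B + control | No | No |

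The two general sentences do not close the last row. An omnibus four-group test shows that some arms differ, without isolating C − A − B + control. A two-sample test, parametric or rank-based, involves two arms at a time, and the interaction involves four.

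**2. The plan's own figure**

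The 30 per group does not follow from the stated inputs alone.
- As proportions, 32% v 52% at one-sided 0.025 and 80% power needs 95 per group.
- As a difference of 20 points in mean percentage reduction, n = 2·SD²·(1.96 + 0.84)²/20², and 30 per group requires an SD of about 27.65. No SD is stated.
- 30/0.75 = 40 and 4 × 40 = 160, so the enrolled number is consistent with a 25% allowance for loss.

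The origin of 30 is a separate matter. Here it shows only that an SD must be assumed. I use 20 to 35 points, which brackets 27.65.

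**3. Standard errors and power**

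For common SD and n per arm, a pairwise contrast has SE = SD·√(2/n) and the interaction has SE = SD·√(4/n). Power by normal approximation is Φ(difference/SE − 1.96), two-sided 0.05. With n = 30:

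| Assumed SD | SE pairwise | SE interaction | Pairwise power, 20 / 10 points | Interaction power, 20 / 10 points |
|---|---|---|---|---|
| 20 | 5.16 | 7.30 | 97% / 49% | 78% / 28% |
| 27.65 | 7.14 | 10.10 | 80% / 29% | 51% / 17% |
| 35 | 9.04 | 12.78 | 60% / 20% | 35% / 12% |

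Example, SD 20 and a 20-point interaction: 20/7.30 − 1.96 = 0.78, and Φ(0.78) = 78%. If all 40 per arm are analysed, interaction power at SD 27.65 is 63% for 20 points and 21% for 10.

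**4. What does not depend on the SD**

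The interaction variance is 4·SD²/n against 2·SD²/n, so for the same difference and power it needs twice the per-group number: 60 against 30 in the plan's own setting.

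**5. How large a synergy is plausible**

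If A and B each reach the planned 52% against 32%, additive effects put C at 32 + 20 + 20 = 72%. A 20-point synergy would then require a 92% reduction, and a 10-point synergy 82%. The 10-point column is therefore the more realistic one.

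**6. Dependence on scale**

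On the ratio scale, with 0.68 of baseline hs-CRP remaining on control and 0.48 on A and B, no interaction means 0.48²/0.68 = 0.34 remaining in C, a reduction of about 66%. On the difference scale, no interaction means 72%. A result between 66% and 72% would therefore be more than multiplicative and less than additive, so the scale has to be fixed before the data are seen.

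**The case against.** The strongest reply is that the article does not confine itself to control comparisons. It says the indices will be compared across all four groups and plans a rank sum test on unspecified pairs, so C against A or B may well be intended. This stands: a reader might infer that the combination will never be compared with the single injections, and the text does not establish that. It is firm only that no such contrast is named and that none of the named tests can test synergy.

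Second, the Background hypothesis is answered by comparisons with control, and in the Objectives *synergistic treatment* may simply label the combination arm. That also stands, so synergy should not be called the trial's only or main question. But the Discussion separately asks whether single and combined injections differ, and if only a label is meant, the word invites a claim that the analysis cannot support.

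Third, a reader might infer that synergy will be declared from differences in significance against control. No passage says so or sets any rule for claiming it. The risk is that nothing in the text prevents it.

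Fourth, contrasts and model terms are often left to the SAP, which is not shown. This limits the severity but does not remove the point, because the article fixes a test, its groups and a sample size that do not match a stated objective.

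Finally, one might say that pairwise analysis wastes half the data on each drug. That is a preference for factorial main effects, which represent each drug's own effect only if there is no interaction. The article declares a parallel design, and this is not a defect.

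**Conclusion.** The point holds in limited form. No interaction test and no C v A or C v B contrast is specified or powered, although the Objectives and Discussion raise both questions. The comparisons with control are valid for the Background hypothesis; they cannot support a claim that the combination is synergistic or better than a single injection.

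Interaction power is modest for a 20-point effect and low for 10 points across the assumed SD range. These figures are illustrative: they rest on an assumed SD, equal across arms, a percentage-point scale, a normal approximation and 30 analysed per arm. The doubling of the required number holds for any common SD. Reading the four arms as a 2×2 layout further assumes that group C gives each injection as groups A and B do; the article states no doses. Severity: should be fixed. It concerns the claims about the combination and leaves the control comparisons intact.

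**What to change.** 1. Keep the comparisons of A, B and C with control.
2. Name C v A and C v B as contrasts, and require both before stating that the combination is better than the single injections.
3. Fit one linear model for hs-CRP to all four arms with astragalus (yes/no), Salvia (yes/no) and their product. Fix one outcome scale in advance, for example log hs-CRP or percentage change, and report the product term with a 95% CI.
4. Write 'synergistic' only if that interval excludes zero in the favourable direction; otherwise write 'combined'. Align the Objectives and Discussion with this rule.
5. Factorial main effects are optional, with a note that they represent each drug's own effect only without interaction.
6. State that the trial was not sized for the interaction and that its power is low, so the estimate and interval carry the information.

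The cost is wording in the analysis section or SAP and one extra model, with no new data or patients. The downside is that the interaction interval will be wide and may leave the synergy question open. The change should be made before unblinding.

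### Quantitative outcomes are compared by an unadjusted two-sample t-test although the hs-CRP effect is a fall from a pre-treatment value; baseline adjustment would add precision at almost no cost

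*Protocol article*

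**What the plan says.** The Statistical analysis section fixes the test for quantitative data: "The comparison of iso-quantitative data between the experimental and the control group will be performed using a student" t-test for two samples. A two-sample rank sum test is also mentioned. Neither has a covariate. The section does not say whether the quantity compared is the post-treatment value, the change or the percentage change.

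Baseline data have one stated use: "a baseline analysis of the demographic characteristics in the four groups of selected cases will be conducted to investigate the balance and comparability across groups". This covers demographic characteristics; baseline hs-CRP is not named.

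The Sample size section takes "hs-CRP as the main effect index" and describes the effect as a reduction: "Conventional Western medicine treatment can reduce hs-CRP by 32" per cent on control, and "it is estimated that Chinese medicine can reduce hs-CRP by 52" per cent on active treatment. Research process record points places a record before treatment: "the screening period (0 days) will be 24 h before recruitment followed by a daily data tracking and recording from day 1 to day 7". The text does not list the assays done at that record, and the schedule (Fig. 2) is not shown.

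**The concern.** Inflammatory markers usually differ widely between patients and tend to persist within a patient, so the pre-treatment value is normally a good predictor of the post-treatment value. A t-test on post-treatment values ignores it. A t-test on change subtracts all of it, which over-corrects unless the two measurements are almost perfectly correlated. Either way, variation that the baseline could explain stays in the error term, in a trial with 30 to 40 patients per group.

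A chance difference in baseline hs-CRP between two arms also carries into the estimated effect. A demographic balance check neither detects nor corrects it.

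The article names a specific test, so the question is whether the stated choice is a good one. It is not a matter of detail left to another document.

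**Working it through.** **Inputs from the article.** Falls of 32% and 52%; 30 per group before losses and 40 after (30/0.75 = 40, so a 25% loss is implied); four equal groups; two-sided tests at 0.05.

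**Inputs not in the article, assumed here.** The correlation ρ between baseline and follow-up; equal variance at the two times; a log-normal marker with log-scale SD 0.8; the percentage falls read as ratios of geometric means. No SD is given, so the 30 per group cannot be used to anchor the variance.

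**1. Information lost by the t-test relative to ANCOVA.** With outcome variance σ², the residual variance is:
- t-test on post-treatment values: σ²
- t-test on change: 2(1−ρ)σ²
- ANCOVA: (1−ρ²)σ²

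The loss is therefore ρ² on post-treatment values, and 1 − (1−ρ²)/[2(1−ρ)] = (1−ρ)/2 on change.

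| ρ | Loss, post-treatment values | Loss, change |
|---|---|---|
| 0.2 | 4% | 40% |
| 0.3 | 9% | 35% |
| 0.5 | 25% | 25% |
| 0.7 | 49% | 15% |
| 0.8 | 64% | 10% |

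Both losses are positive for every ρ strictly between 0 and 1. Which t-test is worse switches at ρ = 0.5. If the better of the two happened to be chosen, the loss would be at most 25%.

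**2. Power, on the log scale.** The effect is ln(0.68/0.48) = 0.348, which is 0.348/0.8 = 0.435 SD. The noncentrality is 0.348/[s√(2/n)], where s is the residual SD:
- post-treatment values: s = 0.8
- change: s = 0.8√[2(1−ρ)] = 0.800 (ρ = 0.5) or 0.620 (ρ = 0.7)
- ANCOVA: s = 0.8√(1−ρ²) = 0.693 or 0.571

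| Analysis | 40 per group, ρ = 0.5 / 0.7 | 30 per group, ρ = 0.5 / 0.7 |
|---|---|---|
| t-test, log post-treatment values | 49% / 49% | 38% / 38% |
| t-test, log change | 49% / 70% | 38% / 57% |
| ANCOVA, log scale, four arms | 61% / 77% | 49% / 65% |

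Simulation at 40 per group agrees within simulation error: about 48-49% for post-treatment values, 47% / 70% for change and 60% / 77% for ANCOVA.

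**3. Scale.** ANCOVA on untransformed values of the same simulated marker gave only about 51% (ρ = 0.5) and 63% (ρ = 0.7). The gain for a skewed marker therefore depends on the log transformation as well as on the covariate.

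**4. Chance baseline imbalance.** The standard error of a two-arm baseline difference, in SD units, is √(2/n): √(2/40) = 0.22 and √(2/30) = 0.26. The 95% ranges are about ±0.44 and ±0.51 SD. A t-test on post-treatment values carries ρ times the difference, and a t-test on change carries (1−ρ) times it in the opposite direction. For a difference of one standard error at 40 per group:
- post-treatment values: 0.224 × 0.5 = 0.11 SD, or 0.224 × 0.7 = 0.16 SD
- change: 0.224 × 0.5 = 0.11 SD, or 0.224 × 0.3 = 0.07 SD

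The assumed effect is 0.435 SD.

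**The case against.** **Validity.** An unadjusted t-test in a randomised trial is unbiased on average, and its standard error already allows for chance baseline differences. This stands. A reader might infer that the planned comparison is biased or invalid, but the document does not support that. Imbalance and lost power are two views of one loss of precision and should not be added together.

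**Size.** A reader might infer a definite loss, such as a quarter to a half of the information. That range needs ρ of about 0.5 to 0.7 and a t-test on raw post-treatment values, and the article states neither. Its percentage-reduction wording points rather to a change-type outcome. On change at ρ = 0.7 the gain in power is about 7 points (70% to 77%), against about 28 points on post-treatment values. This stands and limits the claim to a range.

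**Pooling.** A reader might also object that each two-group test uses only 80 of the 160 patients for its error variance. The effect is negligible: the critical t is 1.991 on 78 degrees of freedom and 1.975 on 156, a difference below 1%. Pooling would also add an equal-variance assumption across arms.

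**Baseline availability.** The visible text does not state that hs-CRP is assayed at day 0. The planned percentage fall requires a pre-treatment value, so the inference is reasonable for hs-CRP. It is unverified for the other markers.

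**Deferral.** Covariates are often left to a statistical analysis plan. Here the article commits to a named test without one, so this objection does not remove the point.

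**Conclusion.** The point holds as one of efficiency. The stated test ignores a pre-treatment value that the trial's own effect definition requires, and under the standard linear model ANCOVA is more precise than a t-test on either post-treatment values or change for any positive ρ below 1.

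The amount gained is not determined by the document. Over ρ from 0.2 to 0.8 the loss runs from 4% to 64% on post-treatment values, or from 40% down to 10% on change. The power figures rest further on the assumed log-SD of 0.8 and on analysis on the log scale. This should be changed, but it does not threaten the validity of the trial.

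**What to change.** In the Statistical analysis section, replace the t-test for hs-CRP, and for each other quantitative outcome that has a baseline measurement, with ANCOVA:
- outcome: the post-treatment value
- terms: treatment arm (four levels) and the same outcome's baseline value
- scale: skewed serum markers log-transformed at both times
- report: each active-versus-control contrast with its 95% confidence interval, as a ratio for logged markers

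Describe baseline characteristics by arm, and do not let a balance test decide whether to adjust. Confirm in the text that hs-CRP is measured at day 0.

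The cost is a few sentences. The model is a standard general linear model in the SPSS software already named. If the day-0 assays are done as inferred, no patients, visits or assays are added. Recruitment is under way, so the change should be made and dated before unblinding.
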